# Designs of two randomized, community-based trials to assess the impact of influenza immunization during pregnancy on respiratory illness among pregnant women and their infants and reproductive outcomes in rural Nepal

**DOI:** 10.1186/s12884-015-0470-y

**Published:** 2015-02-20

**Keywords:** Influenza vaccination, Pregnancy, Early infancy, Influenza like illness, Influenza illness, Birthweight

## Abstract

**Background:**

Among the most important causes of illness and death in both pregnant women and their newborn infants are respiratory infections including influenza. Pregnant women in North America have a 4 to 5 fold excess rate of hospitalization compared to non-pregnant women. Rates of infant hospitalization associated with influenza are much higher than in their mothers. Fully half of children hospitalized for influenza in the US are in the age group 0–5 months, a group where no vaccine is licensed. Data on influenza are much fewer in low income countries where the risks of serious morbidity and mortality are much higher. A recent trial in Bangladesh suggested that influenza immunization in pregnant women could have important protective effects against influenza in both mothers and their infants. These trials were designed to provide additional evidence about the effect of influenza vaccination in pregnancy in settings where influenza may circulate for up to ten months/year.

**Methods/Design:**

We conducted a consecutive pair of community-based, placebo-controlled, randomized trials of influenza vaccination of pregnant women in a rural district in southern Nepal. Two trials were conducted to insure, as much as possible, the match of circulating strains with those included in the vaccine. Eligible women included all who were or became pregnant over a one year period. Each trial included a one year cohort of pregnant women who were individually randomized to the influenza vaccine available at the time of their enrollment or placebo. Exclusions included a history of allergy to vaccine components, prior influenza vaccine receipt, and for the second trial, participation in the first trial. Morbidity was assessed on a weekly basis for women throughout pregnancy and through 180 days post-partum. Infants were followed weekly through 180 days. Primary outcomes included: 1) incidence of influenza like illness in women, 2) incidence of laboratory confirmed influenza illness in infants, and 3) birthweight among newborn infants.

**Discussion:**

We have presented the design and methods of two randomized trials of influenza immunization of pregnant women.

**Trial registration:**

Clinicaltrials.gov: (NCT01034254).

## Background

Pregnancy and delivery are hazardous for mothers and infants in low resource regions, with rates of illness and death many times higher than in wealthier regions. Among the most important causes of these illnesses and deaths in both mothers and infants are respiratory infections including influenza [1]. The best estimates of the clinical significance of complications of respiratory disease during pregnancy are based on indirect data from developed countries [2]. Remarkably few data exist on the prevalence or significance of laboratory-proven influenza infections in pregnant women and the outcomes of infection with influenza in the woman and her fetus, particularly in developing countries [3]. The increased risk of influenza in pregnant women is related to physiologic changes including increases in blood volume, decreases in lung capacity, and attenuation of cell-mediated immune responses [4]*.* Excess mortality with rates approaching 50% were reported in pregnant women during the 1918–19 influenza pandemic, some of the highest rates of any patient group. Influenza was also a leading cause of maternal mortality during the 1957 pandemic [5] and an important cause of maternal morbidity and mortality during the 2009–10 influenza A/H1N1 pandemic [6]. The impact of influenza on the fetus when influenza is contracted during pregnancy is less clear, although cases of stillbirths and fetal deaths have been reported [7] and increased rates of prematurity were documented in the most recent pandemic [8].

A case–control study of US women showed that healthy pregnant women have a four-fold increased rate of hospitalization during influenza season compared to post-partum controls [9]. This indirect evidence has been validated by several studies in the United States and, most recently, by studies in Canada that show a five-fold seasonal increase in the risk of hospitalization among pregnant women [10-12]. Limited data exist documenting influenza infection in pregnant women using laboratory methods, although a study from Britain showed serologic evidence of influenza infection during pregnancy in 11% of 1,659 pregnant women, associated with an overall 43% increased rate of complications in the delivery, postpartum, or newborn infant periods, when compared to uninfected controls [3]. A study of over 6 million hospital admissions of pregnant US women showed that hospitalization with a respiratory illness during pregnancy in influenza season was associated with 4-fold increased risk of preterm delivery and cesarean section, and a 2.5-fold increase in reports of fetal distress, compared to hospitalizations without a respiratory illness [13]. Because of the increased risk of hospitalization, and proven safety of influenza vaccine in pregnant women, routine immunization of all pregnant women during influenza season has been recommended in the US since 1997, and by WHO since 2005.

US infants and children have relatively high rates of illness and hospitalization for influenza infection, despite increasing availability of laboratory diagnostics and the availability of licensed influenza vaccine for this age group [14]. The high rates of illness and hospitalization rates of ~1/1000 prompted the US recommendations in 2004 for universal immunization of infants from 6–59 months. More recently, it has become clear that US infants from 0–5 months of age have a substantial burden of influenza, with hospitalization rates of 0.8 to 1.2% [7,14]. These rates of young infant hospitalization are higher than in other recognized high-risk groups for influenza, such as adults over 60, and much higher than in their mothers. Of all US children under five years of age hospitalized for proven influenza, approximately 50% are in the age group 0–5 months [15], an age group where licensed influenza vaccine is not available. In addition, medically attended illness rates attributable to influenza are 50–100 fold higher than the influenza hospitalization rates in this young infant group [9,14].

Maternal immunization to protect both mothers and their young infants is currently recommended to prevent neonatal tetanus (in limited resource regions) and influenza (in the US, UK, and Canada) [15]. While maternal immunization is a safe and effective strategy with potential to advance both Millennium Development Goals 4 and 5 (child and maternal mortality, respectively), this approach remains underutilized in limited resource regions to prevent illness in mothers and infants [16]. Because the delivery system of antenatal immunization is in place for tetanus toxoid in many low-resource regions, the maternal immunization strategy is programmatically feasible and sustainable for other vaccines [17].

Vaccines with potential to reduce illness of both mothers and infants include influenza, pertussis, and pneumococcal vaccines. These vaccines are known a) to be safe in pregnant women, b) to elicit functional antibody during the period of high risk in mothers, which can then be transferred to the fetus c) deliverable in existing antenatal tetanus toxoid programs, and d) relatively low cost [12]. A recent comparative trial of trivalent inactivated influenza vaccine (TIV) and pneumococcal polysaccharide vaccines in pregnant women in Bangladesh showed substantial protection of both mothers and their infants by maternal immunization with TIV. Maternal influenza immunization reduced laboratory-proven influenza in their infants by 68% from birth to six months of age, and also reduced episodes of maternal influenza-like illnesses (ILI) by 35% [18]. In addition, there were significant improvements in birthweight associated with receipt of influenza vaccine in pregnancy [19]. However, the Bangladesh trial was relatively small and not designed to specifically address the impact of maternal influenza vaccine. Therefore, additional studies to answer this question in a variety of contexts are necessary to inform policy making for immunization programs.

## Methods

### Design

Two, consecutive, individually randomized, placebo controlled trials of influenza immunization during pregnancy were conducted in southern Nepal. Each trial recruited a population-based cohort of pregnant women who were between 17 and 34 weeks gestation over a one year period. The choice of two independent cohorts was used to insure, as much as possible, there would be a match between circulating strains of influenza and that year’s vaccine strains. Two additional substudies were also conducted during these randomized, controlled trials. The first was conducted in a subsample of mother/infant pairs in both trials and assessed the degree to which influenza vaccine produced vaccine-specific antibody in the mothers and the level of antibody transferred to her infant as measured in umbilical cord blood and breast milk. The second was done in a subsample during the first trial and determined the impact of maternal influenza immunization on indirect protection from ILI and laboratory confirmed influenza disease among other household members.

### Study population

The study population for these trials included all married women between 15 and 40 years of age who were identified as pregnant with gestational age between 17 and 34 weeks during a 12-month period in 9 Village Development Committees (VDCs) of Sarlahi District in the terai region of southern Nepal. The terai is the southernmost region of Nepal, lies along the border with India, and is part of the flood plain of the Ganges River and its tributaries that drain from the Himalayas to the Bay of Bengal. Sarlahi District is low and flat (approximately 131 m elevation) with high population density (635/km^2^) [20]. It is typical of the entire Indo-Gangetic plain with a population of over one billion. It is predominately an area of traditional, rural, Hindu culture. The population is mostly peasant farmers (58%) or laborers (26%) and their families and is considered a poor area in Nepal with an estimated poverty gap of 0.47 in 2010 [20].

Pregnant women were identified through a baseline survey of all households at the start of the first trial and subsequently through 5-weekly follow-up of households where women of reproductive age resided. Pregnancy was documented using commercially-available urine pregnancy tests. Only one pregnancy per woman was enrolled. The following pregnant women were excluded in both trials:Women who did not intend to deliver their child within the 9 VDCs in the study area.Women who had already received the current influenza vaccine.Women who were allergic to any component of the vaccine. This exclusion was mostly related to allergies to eggs.Women who refused to provide consent.Women who were later than 34 weeks gestation at the time their pregnancy was identified by the study.Women will be excluded from the analysis of primary outcomes if they deliver their child less than 2 weeks following receipt of the vaccine or placebo.

Two sequential annual cohorts of pregnant women were enrolled into independent trials.

In addition to the exclusions listed above, women who participated in the first trial were not eligible for the second trial.**Eligibility Phase 1:** Women who were pregnant and between 17 and 34 weeks gestation at the time of trial enrollment for the period April 25, 2011 through April 24, 2012 were eligible for participation in the first trial if they were not excluded based on the above mentioned exclusion criteria.**Eligibility Phase 2:** Women who were pregnant and between 17 and 34 weeks gestation at the time of trial enrollment for the period April 25, 2012 through April 24, 2013 were eligible for participation in the second trial if they did not meet exclusion criteria and if they had not participated in the first trial.

The date of trial enrollment for both phases was defined as the day they presented to the vaccination clinic and were randomized.

### Intervention

The intervention tested in these trials was year-round immunization of pregnant women between 17 and 34 weeks gestation with a commercially available, trivalent inactivated influenza vaccine licensed in Nepal. Vaxigrip vaccine (Sanofi Pasteur Ltd.) was used and purchased by the project from the Yetichem Group in Kathmandu, Nepal, which sourced the vaccine from Sanofi India, Mumbai. The vaccine was the current vaccine at the time of enrollment for an individual woman. That is, women were scheduled to receive the most up-to-date influenza vaccine at the time they were enrolled. After the regular change in vaccine, the vaccine was switched to the newly available vaccine. Table 1 shows the dates and formulations of the trivalent vaccines used throughout both study periods. The control group received placebo (saline injection).

**Table 1 Tab1:** **Vaccines used by date**

**Vaccine formulation**	**Vaccine strains**			**Sanofi Pasteur Vaxigrip® lot no.**	**Dates of use**
	**A/H3N2**	**A/H1N1**	**B**		
**Northern 2010-2011**	Perth	California	Brisbane(V)	G7142	24 Apr 11 to 29 Jul 11
**Southern 2011**	Perth	California	Brisbane(V)	H9100	7 Aug 11 to 30 Dec 11
**Northern 2011-2012**	Perth	California	Brisbane(V)	H7099-1	1 Jan 12 to 31 May 12
				H7116-2	1 Jun 12 to 29 Jun 12
**Southern 2012**	Perth	California	Brisbane(V)	J7025-1	1 Jul 12 to 15 Oct 12
**Northern 2012-2013**	Victoria	California	Wisconsin(Y)	J7186-1	15 Oct 12 to 30 Dec 12
**Southern 2013**	Victoria	California	Wisconsin(Y)	J7154-4	30 Dec 12 to 27 Jan 13
				J7217-1	27 Jan 13 to 21 May 13
				K7021-3	21 May 13 to 3 Sept 13
				K7209-3	3 Sept 13 to 9 Sept 13

Women who were in their first trimester of pregnancy (<17 weeks) at the time of pregnancy identification had their enrollment delayed until after 17 weeks. In both groups, tetanus toxoid (TT) immunization status was assessed and if a woman failed to report a history of adequate immunization (i.e. 2 doses during the current pregnancy or 5 total prior doses during her reproductive years), TT was provided in the opposite arm at the same time as the study vaccine (influenza/placebo).

The timing of vaccine delivery differed in the two trials. In the first trial, women were enrolled and vaccinated as soon as they were identified as pregnant and were between 17 and 34 weeks gestation. In the second trial, after pregnancy identification, women were randomly assigned to a week of gestation for enrollment and vaccination that ranged from 17 weeks (or their gestational age at the time of pregnancy identification, which ever was later) to 34 weeks. Vaccine was administered by unmasked study nurses in clinics and homes; these nurses did not participate in the weekly illness assessment of the mother or infant. Mothers and other staff/investigators were masked. At the conclusion of the study, all women randomized to placebo were offered influenza vaccine.

Vaccine and placebo were transported from the supplier in Kathmandu to the field, and from the field study office to vaccination clinic locations in monitored coolers with continuous temperature tracking. Any vaccine not kept within the manufacturer’s recommended temperature range prior to use was discarded.

### Outcomes

There were 3 primary and several secondary outcomes for these trials.

### Primary outcomes

The incidence of laboratory confirmed influenza illness episodes in the infant through 6 months of age.The incidence of low birthweight among newborn infants.Incidence of influenza-like febrile illness (ILI) episodes of the mother during pregnancy and through 6 months postpartum.

Signs and symptoms were ascertained during weekly home visits from the time of maternal enrollment through 180 days following delivery. Every week, field staff visited the home and asked about a series of signs and symptoms for each day in the prior week. For both pregnant and post-partum women, these included fever, persistent cough, sore throat, nasal congestion, myalgia and diarrhea. For infants, these included high fever, cough, difficult or rapid breathing, rhinorrhea, wheeze, dripping ear, diarrhea, difficulty feeding, jaundice and receipt of immunizations. We also ascertained if care was sought for any illness and the type of provider consulted. If a woman or infant had signs/symptoms included in our definitions, a single sterile nasopharyngeal swab with a nylon flocked tip (Copan Diagnostics, Murrieta, CA) was inserted into a nare approximately one-half the distance between the external nostril and the nasal bridge and twisted 360° to obtain a mid-nasal respiratory specimen. It was then placed in Primestore molecular transport medium (Longhorn Vaccines and Diagnostics LLC, Bethesda, MD) and the shaft broken off prior to closing the tube. The test tube was stored at room temperature for up to one week before being transported to the local laboratory. In a subsample of participants, an additional nasal swab was collected from the other nare and placed in viral culture medium.

#### Definitions

**Laboratory Confirmed Influenza in Infants:** An episode of respiratory illness (with one of more of the following: reported or measured fever (axillary temperature >38°C), cough, wheeze, difficult or rapid breathing, or draining ear plus a positive laboratory test for influenza from nasal swab(s).**Low birthweight (LBW) in newborn infants:** The internationally accepted definition <2500 g was considered to be LBW. Eligible weights were those measured within 72 h of delivery. A secondary analysis included a back calculation to the weight at the time of delivery for all infants based on a statistical model developed from longitudinal weight measures from newborns included in a previous study in this population.**Influenza-Like Illness in Mothers (ILI):** The CDC definition of ILI was used that requires reported or measured fever (axillary temperature >38°C) plus either cough or sore throat on one or more days.

Episodes of influenza-like illness were required to be separated by 7 or more symptom-free days. Laboratory-confirmed influenza for both mothers and infants is not simply a subset of ILI, as ILI required fever as part of the definition and respiratory samples were obtained using a broader definition. This broader clinical definition of signs and symptoms included in the definition for laboratory confirmed influenza reflects the need to identify cases of influenza with a lower severity of clinical signs and symptoms than that included with ILI.

### Secondary outcomes

The incidence of clinic visits and hospitalizations for mothers and infants. These were recorded on the weekly morbidity forms and linked to episodes of ILI or respiratory illness.The incidence of ILI and influenza illness in family members. Definitions for ILI and laboratory confirmed influenza will be the same as for mothers and children. Definitions for adults and children 5 years or older will use the maternal definitions. Definitions for children less than 5 years will use the infant definitions.The incidence of ILI in Infants.: We will use a modified CDC definition of influenza-like illness for the infants, including reported or measured fever (axillary temperature >38°C) plus cough, or draining ear, or difficulty breathing occurring on one or more days [2].The incidence of laboratory-confirmed influenza in mothers. This required an episode of respiratory illness (reported or measured fever (axillary temperature >38°C) plus one or more of the following: cough, sore throat, runny nose, nasal congestion, or myalgia), in addition to a positive laboratory test for influenza from a nasal swab.Gestational age. Defined as the difference between the date of birth and the date of the start of the woman's last menstrual period (LMP). LMP was assessed at the time pregnant women were identified. Preterm birth was defined as gestational age <37 completed weeks at the time of delivery.Small-for-Gestational-Age. Infants born small-for-gestational-age were those infants born below the 10^th^ percentile of weight for gestational age [21].Growth. Attained growth was measured at 6 months of age in all enrolled infants. Weight, length, and head circumference were measured and weight-for-age, length-for-age, and weight-for-length Z scores were calculated based on the WHO growth standards [22].Causes of Febrile Illness: Causes of ILI and respiratory infections were defined based on virologic and pertussis assays taken from nasal swabs.

### Randomization

Pregnant women were individually randomized to either intervention or control at the time of enrollment. Enrollment was defined as the date on which the women was randomized and received her assigned “treatment”. In phase 1 (April 25, 2011 – April 24, 2012) vaccination was scheduled as soon as possible after 17 weeks gestation or at 17 weeks if the pregnancy was identified prior to 17 weeks. Randomization was stratified by VDC and gestational age (GA) (two strata 17–25 weeks, 26–34 weeks) in blocks of size 8. In phase 2 (April 25, 2012 - April 24, 2013), randomization was stratified by VDC and gestational age (GA) (two strata 17–25 weeks, 26–34 weeks) and in blocks of size 8. For both phases, individual envelopes were prepared with a sequential serial number on the outside of a sealed envelope (separate set of ordered envelopes for each VDC-Gestational Age stratum in both phases and the treatment assignment for that participant was printed on a piece of paper inside the envelope). When a woman of child-bearing age was identified as pregnant, she was given an appointment date to be formally enrolled and receive her assigned treatment. Upon arrival at the clinic, she had her eligibility reconfirmed and then was listed on a sequential vaccination receipt log specific to her VDC-Gestational Age stratum. Once in the vaccination room, the assigned sealed envelope was opened and she received the treatment (code A, B C, or D) found inside. At the clinic, vaccine and placebo were pre-coded and the appropriate vaccine was provided to the participant based on the code contained in her pre-numbered envelope.

### Data collection

The timing of data collection activities is outlined in Table 2 and described in more detail below.

**Table 2 Tab2:** **Data collection schedule**

**Data items**	**Pregnancy identification**	**Vaccine delivery**	**Weekly during pregnancy**	**Monthly during pregnancy**	**Delivery**	**1 month**	**3 month**	**6 month**	**Weekly through 6 months post-partum**
Mother’s Demographic and SES Characteristics	X								
Mother’s Reproductive History	X								
Mother’s Anthropometry	X								
Maternal Vaccination Receipt		X							
Labor & Delivery Characteristics					X				
Infant Weight, Head Circumference					X			X	
Maternal Vital Status			X		X				X
Maternal Morbidity			X		X				X
Maternal Nasal Swab									X If indicated
Maternal Pregnancy Related Morbidity				X					
Maternal Temperature				X	X				
Maternal Weight, Blood Pressure, Pulse	X			X					
Infant Vital Status					X				X
Infant Morbidity					X				X
Infant Nasal Swab									X if indicated
Infant Temperature					X				
**Substudy #1 (Antibody Transfer)**									
Maternal pre & post vaccine blood samples	X (pre)				X (post)				
Infant cord blood sample					X				
Maternal breast milk sample						X	X	X	

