#### Pregnancy Identification

Initial identification of pregnant women occurred at the baseline household visit prior to phase 1. Subsequently, all married women between 15 and 40 years of age were visited every 5 weeks and asked about their menstrual period in the preceding 5 weeks. If the woman had her period, the week of the period was recorded and she was visited again 5 weeks later. If she reported no menstrual period, she was offered a urine-based pregnancy test at her home. If the test was positive, she received a pregnancy enrollment interview that included her reproductive history, morbidity in the previous month, date of her last menstrual period, tobacco and alcohol use, and plans for where and by whom she would deliver her baby. We also measured her weight, height, blood pressure, temperature and pulse. Pregnant women were encouraged to attend antenatal care clinics in the public or private sector and to deliver at a certified birthing facility. The study provided education on nutrition, clean delivery, and danger signs at this visit. We also provided her with 90 days of iron-folic acid supplements, a clean birthing kit (included a clean blade, string, plastic tarp, and small plastic disc on which to cut the cord), chlorhexidine ointment for umbilical cord antisepsis, and a single dose of albendazole.

We visited all women monthly throughout their pregnancy to collect pregnancy-related morbidity in the previous month ask about tobacco and alcohol use, and to measure weight, blood pressure, pulse, and temperature.

At the time of pregnancy identification, information on household characteristics was collected and included measures of household socioeconomic status using an asset index, ethnicity, total number of persons in the household, house construction materials and size, source of drinking water, household sanitation practices, type of fuel used for cooking, and whether there were members of the household working outside the local area or country. A complete household roster was also completed at this time including information on age, date of birth, sex, marital status, literacy, educational level, and tobacco use for each member of the household.

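### The antibody substudy's pre-vaccine serum is scheduled at pregnancy identification rather than at vaccination, so for women identified early the baseline is weeks to months old and absorbs infection before the injection

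*Protocol article*

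**What the plan says.** The Design section says that the first substudy, run in a subsample of both trials, "assessed the degree to which influenza vaccine produced vaccine-specific antibody in the mothers", together with transfer to the infant through cord blood and breast milk.

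Table 2 is the only place that times the maternal blood. The row "Maternal pre & post vaccine blood samples" has its pre mark in the pregnancy-identification column and its post mark in the delivery column. The table has a separate vaccine-delivery column and uses it for "Maternal Vaccination Receipt", but that cell is blank in the blood-sample row. Neighbouring rows confirm the alignment: cord blood falls under delivery, and breast milk under 1, 3 and 6 months.

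On the interval from identification to injection:
- Pregnancy Identification: women were "visited every 5 weeks and asked about their menstrual period in the preceding 5 weeks", with a urine test when a period was missed.
- Intervention: women below 17 weeks "had their enrollment delayed until after 17 weeks".
- Intervention, first trial: "women were enrolled and vaccinated as soon as they were identified as pregnant and were between 17 and 34 weeks gestation".
- Intervention, second trial: "women were randomly assigned to a week of gestation for enrollment and vaccination that ranged from 17 weeks", or from the current gestational age if later, up to 34 weeks.

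Randomization takes place on the day of vaccination, against saline placebo (Intervention; Randomization).

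**The concern.** A pre-vaccine titre is meant to describe the woman at the moment of injection. Five-weekly visits with a urine test after a missed period can find a pregnancy well before 17 weeks, and a blood sample taken then ages until the vaccination visit. The Abstract describes settings where influenza may circulate for most of the year, so some women will be infected in that interval. Their infection-induced antibody then appears as part of the rise from the pre sample to the post sample.

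At stake is the reading of the substudy. A fold-rise or seroconversion rate within the vaccine arm would mix vaccine response with earlier natural infection, and seropositivity labelled pre-vaccine would not be seropositivity at injection. An older titre should also predict the delivery titre less well, which costs precision when it is used as a covariate.

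**Working it through.** The article gives no substudy sample size, power or gap length, so there is no stated figure to reproduce. The check has four steps.

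**1. Length of the gap.** Vaccination weeks come from the Intervention section. With identification at week *i*, the first-trial gap is max(17, *i*) − *i*. The second-trial gap runs from max(17, *i*) − *i* to 34 − *i*. Its mean is (max(17, *i*) + 34)/2 − *i* if weeks are assigned uniformly (assumption). Clinic scheduling delay is ignored.

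| Identified at week | Trial 1 gap | Trial 2 range | Trial 2 mean |
|---|---|---|---|
| 5 | 12 | 12–29 | 20.5 |
| 10 | 7 | 7–24 | 15.5 |
| 15 | 2 | 2–19 | 10.5 |
| 20 | 0 | 0–14 | 7.0 |
| 30 | 0 | 0–4 | 2.0 |

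The article does not give the distribution of gestational age at identification, so no average gap for a whole trial can be calculated.

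**2. Share infected in the gap.** The Background cites a British study with serologic evidence of infection in 11% of pregnancies. Applying that to Nepal, evenly over 40 weeks, is an assumption: p(g) = 1 − 0.89^(g/40).
- g = 2: 0.6%
- g = 7: 2.0%
- g = 12: 3.4%
- g = 24: 6.8%
- g = 29: 8.1%

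A deliberately high alternative treats every influenza-like illness at the planning rate of 34/100 person-years (Sample size) as influenza: p(g) = 1 − exp(−0.34 g/52.18). It gives 4.5% at 7 weeks, 14.5% at 24 and 17.2% at 29.

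**3. Effect on mean titres.** Assume a true vaccine rise of 1.5 log2 units and a natural boost of 2 log2 units. The rise within the vaccine arm is then 1.5 + 2p, and within placebo 2p.
- Gap 0: 1.50 and 0.00, difference 1.50
- Gap 12 weeks: 1.5 + 2 × 0.034 = 1.57 and 0.07, difference 1.50
- Gap 29 weeks: 1.5 + 2 × 0.081 = 1.66 and 0.16, difference 1.50

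A simulation of 200,000 women gave the same values. Gap infections precede randomization, so they are balanced between arms in expectation.

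**4. Effect on seroconversion.** A woman already counted through gap infection cannot be counted again. With true vaccine seroconversion v, the vaccine arm reads (1 − p)v + p, placebo reads p, and the difference is (1 − p)v. Take identification at week 8 (assumption), so that the mean second-trial gap is 25.5 − 8 = 17.5 weeks and p = 1 − 0.89^(17.5/40) = 5.0%. With v = 60% (assumption):
- Vaccine arm: 0.95 × 0.60 + 0.05 = 62%
- Placebo: 5%
- Difference: 57 points instead of 60

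The proportional loss equals p whatever v is. With the high alternative, p = 10.8% and the difference is 0.892 × 60 = 53.5 points.

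**The case against.** Several arguments limit the point, and most of them stand.

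**The gap is not long for everyone.** First-trial women identified at 17 to 34 weeks were vaccinated as soon as they were identified, and in the second trial the assigned week can coincide with identification. This stands. The delay of weeks to months applies to women identified before 17 weeks and to many in the second trial.

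**A reader might infer that the substudy has no pre-vaccine baseline at all.** The documents do not support that. The sample precedes both vaccination and randomization, so it is a valid though dated covariate. What is missing is a titre at the time of injection.

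**A reader might infer that the two trials' antibody results cannot be compared because the second trial delays vaccination.** That does not follow. Natural infection enters the rise over the whole interval between samples, which here runs from identification to delivery in both trials. With identification at week 8 and delivery at week 40, it is 32 weeks and 1 − 0.89^(32/40) = 8.9% in each.

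**Drawing blood at vaccination leaves some of the problem.** This stands, because the post sample is taken at delivery. On the same assumptions, vaccination at week 17 leaves 23 weeks (6.5%) in the first trial, and the mean second-trial week of 25.5 leaves 14.5 weeks (4.1%). Moving the draw therefore makes the two trials' windows unequal.

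**The controlled comparison is sound.** This stands for mean titres. It does not fully hold for seroconversion, where the difference shrinks as shown under working.

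**The article names no fold-rise or seroconversion endpoint, and Table 2 is loosely drawn.** Both are true. Table 2 marks maternal nasal swabs only post-partum, although the Primary outcomes section has them taken from symptomatic women in general. It also omits maternal temperature at identification, which the Pregnancy Identification section says was measured. The accounts of the identification and vaccination visits mention no blood draw, and Laboratory procedures gives the method without the timing. A misplaced mark is possible. Even so, the only published statement of timing is then wrong and needs correcting.

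**Conclusion.** The point holds in limited form. As published, Table 2 places the pre-vaccine serum at pregnancy identification. For women identified early this is well before the injection, with the longest gaps in the second trial. Individual rises and within-arm seroconversion then include some infection before vaccination. A between-arm seroconversion difference is diluted slightly: about 3 points out of 60 in the second trial, given identification at week 8, uniformly assigned weeks, an 11% infection risk per pregnancy and 60% vaccine seroconversion. The baseline is also a weaker covariate; the article gives nothing from which to quantify that loss.

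The vaccine-minus-placebo difference in mean titres and the delivery and cord titres remain unbiased. The three primary outcomes are not touched. This is a cheap improvement to a substudy and does not threaten the trials' main conclusions.

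**What to change.** In Table 2, move the pre-vaccine blood sample from pregnancy identification to vaccine delivery, drawn at the enrolment/vaccination visit immediately before the injection in both trials. Keep the delivery sample. The gap then becomes zero, and the titre describes the woman at injection.

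The cost is small. The same venipuncture moves to a visit the woman already attends, with a blood kit and cooler needed there for the subsample. It also avoids drawing blood from women who never reach enrolment, a number the article does not give. Infection between injection and delivery still contributes to the rise, over a window that will differ between the trials, so placebo remains the reference.

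Second-trial enrolment closed in April 2013, so for these two trials the remedy lies in the analysis and the record:
- If sera were drawn at identification, make the substudy result the between-arm comparison of delivery titres, adjusted for the earlier titre. Do not present within-arm rise as vaccine response. Report the sample-to-injection interval by trial.
- If the Table 2 entry is a slip, correct it and state when the sample was actually drawn.
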